### **Secondary objectives**

- 2.1 To characterize the health status of the population of HIV+ pregnant women seeking antenatal care at the Gugulethu Midwife Obstetric Unit (MOU) including maternal and infant outcomes
- 2.2 To describe uptake and timing of services received throughout the PMTCT cascade, including antenatal ART initiation and follow-up, at the Gugulethu MOU
- 2.3 To examine whether there is variation in the impact of the two postpartum HIV care strategies on the primary outcome between subgroups of women according to their demographic, clinical and psychosocial characteristics, measured antenatally and postnatally.
- 2.4 To describe changes in women's clinical and/or psychosocial characteristics between the antenatal and postnatal periods, and investigate how these are independently associated with the primary outcome
- 2.5 To compare MCH-focused ART services to general adult ART services on:
  - a. Women's missed visits and loss to follow-up on ART up to 18 months postpartum
  - b. Breastfeeding practices, including duration of exclusive feeding and weaning patterns
  - c. Maternal viral suppression throughout the breastfeeding period as well as before and after cessation of breastfeeding
  - d. Infant health outcomes including growth parameters and incidence of respiratory and/or diarrhoeal illness
  - e. Rates of HIV transmission from mother-to-child at 6 weeks and 12 months postpartum
  - f. Acceptability of different strategies for delivering HIV care and treatment during the postpartum period
  - g. Cost-effectiveness in delivering HIV care and treatment during the postpartum period
  - h. Developmental scores of 1 year old infants

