#### *Phase 3: Subset of Phase 2 participants eligible for randomization*

- Consented and participated in Phase 2
- Initiated ART during the antenatal period
- Currently breastfeeding within <7 days postpartum (with an allowable window of up to 28 days postpartum)
- Willingness to be randomized and return for postnatal study visits
- Able to provide informed consent for research (Informed Consent #3)

*Infant neurodevelopmental assessment: Infants of women completing the 12 months postpartum visit*

- Completed participation in Phase 3
- Infant does not have any major congenital anomaly
- Infant is not known to be HIV infected at age 12 months

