#### General adult ART management strategy

Women and infants randomized to the general adult ART management strategy will receive postpartum ART services according to the local standard of care. Specifically, women will be referred from the MOU ART service to their nearest adult ART clinic at their first postpartum ART clinic visit, at around 6 weeks postpartum. The precise timing of this referral will depend on the scheduling of women's ART visits, and may take place between approximately 4 and 8 weeks after birth. Infants will be referred for routine infant care to local primary care clinics, following standard of care in this setting.

The specific facility women are referred to will be determined by their area of residence. For women who reside within Gugulethu itself, referral will be to the ART service at the Gugulethu CHC (located approximately 100 metres from the MOU; this applies to approximately 60-70% of women attending the MOU); the corresponding infant referral is to one of four primary care clinics in the local community. For women who live in other communities (with the Gugulethu MOU as their closest antenatal clinic, but not their closest ART clinic), referral will be to their nearest adult ART clinic, primarily facilities serving the communities of Philippi and Nyanga. All infants will be referred to their nearest routine infant follow-up service. Women may be referred to other facilities (e.g., in other parts of Cape Town or in the Eastern Cape) upon request.

In addition, midwives working in the MOU-ART service may opt to refer a woman to a higher level of medical care (e.g., if there is concern regarding ART toxicity) or on the basis of clinical or psychosocial grounds (if there are concerns regarding non-adherence). Reasons for deferred or alternate referral are documented in the clinical record.

On the day of referral, all women receive counselling on long-term ART adherence, the ongoing risks of MTCT through breastfeeding, and the need for repeat infant HIV testing. Following provincial protocols, referrals employ a Western Cape ART transfer form, completed in duplicate. The original form is sent with the patient, and the copy is retained in the patient's MOU folder. Patients are prescribed one month of treatment and advised to make an appointment at their referral clinic as soon as possible before their one-month ART supply is finished.

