### *Randomization*

Randomization will take place at the end of the study measurement visit within the first week postpartum. Randomization will follow a dynamic permuted block design. Randomization numbers will be generated prior to the start of the study, and placed in sequentially numbered opaque envelopes. Randomization envelopes will be stored in a locked cabinet in the study office at UCT that will be accessed by the study coordinator when a woman is fully consented and has completed the immediate postpartum study visit, with independent documentation of the participant ID number, randomization date, and randomization assignment. The study coordinator will provide the MOU-ART service with a regularly updated list of women to be retained within the MOU-ART service until they have ended breastfeeding. The study coordinator involved in randomization will not be involved in interviewing participants.

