| Trauma/abuse assessment                   |                                                           | X                                                               |                                                          | X                                                                   |                                                                           |                                        |                                        |                                        | X                                        |                                          |
| Social impact scale                       |                                                           | X                                                               |                                                          |                                                                     | X                                                                         |                                        |                                        |                                        | X                                        |                                          |
| Availability of social support scale      |                                                           | X                                                               | X                                                        |                                                                     |                                                                           |                                        | X                                      |                                        | X                                        |                                          |
| Infant feeding intentions/practices       |                                                           |                                                                 | X                                                        | X                                                                   | X                                                                         | X                                      | X                                      | X                                      | X                                        | X                                        |

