#### Data analysis

Data will be exported to Stata Version 12.0 (Stata Corporation, College Station, Texas) or R (Gnu Project) for analysis. All analyses will be carried out under supervision by the study statistician. All outcomes will be blinded to investigators until the data are cleaned and data analyses completed.

As described above, the primary analysis population (up to n=390) is all women enrolled into Phase 3 of the study who initiated ART during pregnancy after 1 July 2013 when the new provincial PMTCT guidelines were implemented. The subset of women in Phase 3 who initiated ART before this time (n=90, approximately) will contribute to a secondary analysis population comprised all women initiating ART in pregnancy and enrolled into Phase 3 during the study period (up to n=480).

For the primary objective, we hypothesize that women in the MCH-focused ART group will be more likely to be retained in care (defined as attending ART clinical appointments and/or medication refill visits in the window between 9 and 12 months postpartum) and maintain viral suppression (defined as <50 copies/mL, with secondary analyses at other thresholds) at 12 months postpartum, compared to women randomized to the general adult ART group. Comparisons of study groups at enrolment will be stratified by duration of ART during antenatal period (i.e., prior to randomization), and will examine demographic and HIV-related variables. Comparison of outcomes will be based on Fisher's exact test, comparing the proportion of women in each arm reaching the primary endpoint and its components; all statistical tests for the primary analysis will be two-sided at  $\alpha=0.05$ . Analyses will be by intention-to-treat, with secondary analyses stratified by duration of postnatal follow-up in the MCH-ART arm. The duration of viral suppression during the postpartum period will be defined as cumulative study time with a documented VL<50 copies/mL (with sub-analyses for <400 and <1000 copies/mL). Kaplan-Meier methods stratified by study group will be used to describe time to detectable viraemia and time to defaulting care, with proportional hazards models used to examine the independent influence of participant characteristics. Note that primary analyses will draw only on women enrolled into Phase 1 and initiating ART after 1 July 2013; women initiating ART before this time will be included as a secondary analysis population for selected analyses.

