Secondary objective 2.4 will be addressed through analyses of the association between demographic, psychosocial and clinical measures (including characteristics of antenatal ART use) on the primary outcome. Analyses will parallel the pure count and time-to-event methods described for the primary objective. In addition, we will use proportional hazards models to identify measures independently associated with the primary outcome and its constituents; variable selection will be based on directed acyclic graphs developed *a priori* to help distinguish causal intermediates from confounding variables (for instance, antenatal ART adherence may be a causal intermediate through which demographic or psychosocial characteristics influence the primary outcome, rather than a confounder). All regression analyses will include trial arm as a covariate; other aspects of model building and diagnostics will follow standard approaches. Outputs will be expressed as hazard ratios and 95% confidence intervals.

Comparison of secondary outcomes between the two postnatal ART services will employ both pure count and person-time methods, as described above. Patterns of women's missed visits during the postpartum period (objective 2.5.A) will be analysed according to the frequency of different numbers of missed/late visits, and the timing of the missed/late visits during the postpartum. Breastfeeding practices (objective 2.5.B) will be analysed according to the duration of exclusive breastfeeding from birth; the duration of mixed feeding; and the timing of final infant exposure to breastmilk. Maternal viral suppression (objective 2.5.C) will be analysed according to the frequency and timing of detectable viraemia (with cutpoints at <50 and <1000 copies/mL) as well as 'survival' to detectable viraemia through 12 months. Incidence of infant respiratory and/or diarrhoeal illness (objective 2.5.D) will be analysed using person-time methods; comparisons of infant growth parameters will use dependent (intra-child) and independent (between child) comparisons. Rates of mother-to-child transmission will be compared at 6 weeks and 12 months using pure count methods (objective 2.5.E).

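### Exclusive-breastfeeding duration is compared between arms from birth, so any exclusive period that ended before randomisation is counted as an outcome and dilutes this secondary comparison

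*Protocol*

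**What the plan says.** Secondary objective 2.5.b compares the two services on "Breastfeeding practices, including duration of exclusive feeding and weaning patterns". The Data analysis section states that "Comparison of secondary outcomes between the two postnatal ART services will employ both pure count and person-time methods", and that breastfeeding practices "will be analysed according to the duration of exclusive breastfeeding from birth", together with the duration of mixed feeding and the time of last exposure to breastmilk. No analysis set is named for this outcome. The general statement, made in the paragraph on the primary objective, is "Analyses will be by intention-to-treat".

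The feeding criterion for Phase 3 is "Currently breastfeeding within <7 days postpartum (with an allowable window of up to 28 days postpartum". Exclusive breastfeeding is not required there, in the exclusion criteria or in the Phase 3 procedures. On timing, the Randomization section says "Randomization will take place at the end of the study measurement visit within the first week postpartum". Feeding is asked at that same visit: Section 8 lists infant feeding among the visit 4 instruments, and the schedule marks "Infant feeding intentions/practices" at visit 4.

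**The concern.** The clock for this outcome starts at birth, but allocation comes days later, and in the extreme up to four weeks later. A woman who gave other feeds before visit 4 completed her exclusive period before she had an arm. Her value cannot depend on the service she is assigned to, yet it enters the arm contrast as an outcome. Such values add variance and no expected difference, so the estimated difference is pulled toward zero and power falls.

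Arm B includes a review of infant feeding at each postpartum clinic visit, so feeding is an outcome the intervention could plausibly move. The variable that identifies the affected women is collected just before randomisation, but the stated analysis does not use it.

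**Working it through.** **Plan's own figure.** There is none for this outcome. The 90% power and the total of 292 in Sample size considerations belong to the primary endpoint and say nothing about feeding.

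**The sequence of events.**
1. Time origin: birth (Data analysis).
2. Entry: currently breastfeeding, exclusive or not; nominal limit 7 days, outer limit 28 days (Phase 3 inclusion criteria).
3. Visit 4: feeding recorded (Section 8, Phase 2; schedule).
4. Randomisation: after the visit 4 measurements.
5. Arm A referral out of the antenatal-clinic service: "may take place between approximately 4 and 8 weeks after birth".

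Exclusive periods that end between steps 1 and 3 precede allocation. Those that end between steps 4 and 5 follow allocation but fall before the services differ much.

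**Illustration 1: log-rank test.** Inputs: two-sided alpha 0.05 and, borrowed for illustration, 90% power on the endings after randomisation. Assumption: a share s of all D endings precedes randomisation. With log hazard ratio θ and 1:1 allocation:
- women still at risk only: expected Z = θ·√(D(1−s)/4)
- all women: expected Z = [θ·D(1−s)/4] / √(D/4) = θ·(1−s)·√(D/4)
- ratio, all to restricted: √(1−s)

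The Z for 90% power is 1.960 + 1.282 = 3.242. Power in all women is Φ(3.242·√(1−s) − 1.960):

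| s (assumed) | Z | power |
|---|---|---|
| 5% | 3.160 | Φ(1.200) = 88% |
| 10% | 3.076 | Φ(1.116) = 87% |
| 20% | 2.900 | Φ(0.940) = 83% |

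**Illustration 2: proportion still exclusive at a later time.** Assume 30% versus 45% among women exclusive at randomisation, 146 women per arm (292/2), and a share m of women already mixed feeding. In all women the difference is (0.45 − 0.30)·(1−m).
- m = 10%: 40.5% − 27.0% = 13.5 points; power 69% in all women, 71% in the restricted set.
- m = 20%: 36.0% − 24.0% = 12.0 points; power 61% against 66%.

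**Dependence on the method.** In a simulated rank-sum comparison of durations (exponential means of 12 and 18 weeks after a 4-week window, 146 per arm), power was 67% in all women against 80% restricted at m = 10%, and 49% against 75% at m = 20%. The protocol names neither this test nor the log-rank for feeding. The direction is the same under each method, but the size is not.

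**The case against.** Counting exclusive breastfeeding from birth is the ordinary definition, and an unrestricted intention-to-treat comparison is valid. Randomisation balances the pre-randomisation endings in expectation. That stands: a reader might infer bias toward one arm or a raised type I error, and the documents support neither. Only precision is lost.

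A reader might also take day 28 as the usual time of randomisation. It is the outer limit. The Randomization section places it in the first week, and Section 8 ties visit 4 to a routine visit at 2–4 days postpartum, so the affected share may be small.

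That the comparison covers all randomised women is an inference from the intention-to-treat sentence and the absence of any restriction. The sentence on feeding does not say so. A statistical analysis plan might add a restriction, but the time origin at birth is fixed in the protocol itself.

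It can be argued that a woman might give an early feed and return to exclusive breastfeeding, so that arm could still affect her. A duration counted from birth answers this: the period starting at birth has already ended.

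Finally, restricting on visit 4 status leaves in the endings between randomisation and Arm A referral, which also dilute the contrast. That is correct, and they should stay, because removing women on events after randomisation would break the randomised comparison.

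**Conclusion.** The point holds as an avoidable loss of precision in one secondary outcome for which the protocol states no power. Exclusive periods that ended before allocation count toward an arm contrast they cannot inform. A difference in means or proportions shrinks by the factor (1−m), and a log-rank statistic is multiplied by √(1−s) relative to the restricted comparison.

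Neither m nor s can be estimated from the protocol. At assumed shares of 5% to 20% the log-rank illustration loses roughly 2 to 7 points from 90% power. Larger losses can be produced by assuming larger shares or another test, but nothing in the document supports choosing them. The primary endpoint is unaffected.

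**What to change.** In the paragraph on objective 2.5.B:
- keep duration of exclusive breastfeeding from birth in all randomised women, as a descriptive summary by arm;
- base the arm comparison on time from randomisation to the end of exclusive breastfeeding, among women recorded as exclusively breastfeeding at visit 4;
- report by arm the number and share already mixed feeding at visit 4;
- leave the timing of last breastmilk exposure in all randomised women, as the protocol already provides.

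Because visit 4 feeding status is measured before allocation, the restriction preserves the randomised comparison. It needs no new data, provided that the visit 4 instrument shows whether any other feed has been given since birth. The form itself is not in the text at hand, so this should be checked.

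The cost is a change of wording and a slightly smaller set for one secondary comparison. Its result then applies to women exclusively breastfeeding at randomisation, and the report should say so.

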Overall, a total of approximately 1600 HIV+ pregnant women will participate in Phase 1 of the study over 12 months. From this group, it is anticipated that approximately 600 HIV+ pregnant

women eligible for ART will be identified as eligible for Phase 2 participation. We estimate that of the approximately 600 women on ART followed in Phase 2, approximately 480 will be eligible for and enrolled into Phase 3 and randomized to one of two postpartum ART delivery strategies.

Follow-up of all participants in Phase 3 will end at 18 months postpartum. The total length of participation will vary based on gestational age at enrolment into Phase 2, ranging from a minimum of approximately 52 weeks to a maximum of approximately 80 weeks. The study schema is summarized in the diagram below.

Figure 1: Study Schema

[figure not shown]

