## **6. Antenatal PMTCT and ART Services at the Gugulethu MOU**

Phase 1 (cross-sectional study) and Phase 2 (cohort study) take place during the antenatal period, and will observe women receiving routine PMTCT and ART services at the Gugulethu MOU. All services will follow the local standard of care. Briefly:

- At the first ANC visit, all pregnant women undergo the following procedures:
  - routine blood testing (including ABO blood group, syphilis screening and haemoglobin) sent to the National Health Laboratory Services (NHLS) laboratory
  - medical and obstetric history and examination performed by a nurse-midwife
  - Rapid HIV testing, with pre/post-testing counselling
    - Women who are HIV-infected receive counselling, undergo venesection for serum creatinine and CD4 enumeration, and then women not already taking ART are started on a triple-drug antiretroviral regimen immediately, per local PMTCT guidelines.
    - Breastfeeding counselling begins at the first antenatal care visit, with all women encouraged to exclusively breastfeed for 6 months. Follow-up counselling is provided throughout the antenatal period.
    - Pregnant women receiving ART at the MOU return 1-2 monthly for follow-up visits and medication refills until delivery. Women already receiving ART elsewhere, continue their care at their current ART clinic.
- Labour and delivery take place at either the Gugulethu MOU or nearby obstetric hospitals. All women make a routine postnatal visit to the Gugulethu MOU within 7 days postpartum; this is the only form of maternal postnatal care in this setting.

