#### MCH-focused ART management strategy

Women randomised to the MCH-focused ART management strategy will be retained in the MOU-ART service, along with their infants, throughout the period of breastfeeding, and referred to their nearest adult ART clinic (as described above) only after the end of breastfeeding. ART visits will be scheduled 1-2 monthly throughout this period. At each clinic visit during the postpartum period, mothers and infants will receive:

- Routine ART care, following local protocols
- Review of infant feeding practices specifically
- Routine infant health care (including infant weight monitoring, vaccination and early infant HIV diagnosis) with completion of the infant's Road-to-Health Card. This is the identical set of services to those provided through local primary care clinics; in all instances, there is referral to local paediatric services when required
- Ongoing PMTCT counselling, including messaging on ongoing transmission risk during the postpartum period; ART adherence; safe infant feeding practices; adherence to daily nevirapine prophylaxis (through 6 weeks postpartum per local guidelines); and the need for infant HIV testing at 6 weeks postpartum and again after cessation of breastfeeding

At each postpartum visit, mothers will be asked basic questions on infant feeding practices related to current feeding practice, plans for weaning and future feeding intentions. Mothers who are found to have not breastfed for at least 1 week before a clinic visit, and who do not state an intention to resume breastfeeding, will be eligible for referral out of the MOU ART service. Referrals out of the MOU ART service will follow the guidelines described above. For mothers who are referred out of the MOU, infants will be referred to their nearest routine infant follow-up service.

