***Eighteen month postpartum visit (study visit 11)***

Mother-infant pairs in both trial arms will be seen at 18 months postpartum. At this visit (lasting 60 minutes):

- Questionnaires will be administered on recent maternal, child and HIV-related health care, HIV disclosure and ART use (including side effects and adherence). Additional instruments will collect data on maternal family planning, future pregnancy intentions, and mental health measures, infant feeding practices, and infant health and health care.

- Mothers will undergo phlebotomy to draw 5mL of venous blood for storage and batched viral load testing.
- Mothers weight and mid-upper arm circumference will be measured
- Growth parameters of the infant will be measured ( weight, length, head circumference and mid-upper arm circumference)
- Infants who are not known to be HIV-infected will undergo phlebotomy. No more than 5mL of venous blood will be drawn and used to conduct a rapid antibody test. For those infants who are reactive via antibody test, additional HIV PCR testing will be conducted with storage of remaining specimen. Results of this HIV testing will be returned to mothers by study staff, with urgent recall of any infant found to be infected for referral to clinical care.

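### The objective 2.5.c viraemia curve stops at 12 months and so leaves out the 18-month viral load already scheduled in both arms

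*Protocol*

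**What the plan says.** Objective 2.5.c (section 2, Secondary objectives) compares the arms on "Maternal viral suppression throughout the breastfeeding period as well as before and after cessation of breastfeeding". It sets no time limit.

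Section 10, Data analysis, gives two analyses for it. One is the frequency and timing of detectable viraemia, with no stated end. The other is a survival analysis "to detectable viraemia through 12 months". No reason is given for that horizon, although it matches the time of the primary endpoint.

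Section 3, Overview, states: "Follow-up of all participants in Phase 3 will end at 18 months postpartum". The eighteen-month visit in section 8 applies to both arms and includes the maternal sample: "Mothers will undergo phlebotomy to draw 5mL of venous blood for storage and batched viral load testing". The Schedule of study measurements also marks a viral load at 18 months.

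Arm A transfers to general adult services at about 4-8 weeks postpartum. Arm B women are "referred to their nearest adult ART clinic (as described above) only after the end of breastfeeding".

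**The concern.** Objective 2.5.c asks in part what happens to suppression once breastfeeding has stopped. Cessation varies between women, so a fixed 12-month end gives early weaners several samples after cessation and late weaners one or none. In Arm B, cessation also triggers the move to general adult services, so a late weaner's move falls near or past the end of the curve.

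The sample that would fill this gap is drawn anyway. What is at stake is how well one secondary analysis answers one part of its objective. The primary endpoint is fixed at 12 months and is not touched.

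**Working it through.** **Plan's own figure.** The Protocol's total of 292 (10% v 25%, 90% power, two-sided 0.05) reproduces exactly with the continuity-corrected two-proportion formula. 292/390 = 0.749, so the enrolment target of 390 implies about 25% loss by 12 months. The point does not depend on 292; the 25% is reused below.

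**Scheduled viral loads after cessation.** The Schedule marks 6 weeks and 6, 9, 12 and 18 months. The 3-month visit text also describes a viral load sample, but the Schedule leaves that cell blank; this does not affect the rows below.

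| Weaning age | Samples after cessation, curve to 12 months | Curve to 18 months |
|---|---|---|
| 6-9 months | 2 (9, 12) | 3 |
| 9-12 months | 1 (12) | 2 |
| 12-18 months | 0 | 1 |

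This count is the same in both arms for a given weaning age.

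**Arm B samples after transfer.** Referral needs at least 1 week without breastfeeding (section 7, MCH-focused strategy) and the infant's final HIV status, with the PCR 2-4 weeks after cessation (section 7, Infant follow-up). Taking 1-4 weeks at 4.345 weeks per month gives 0.23-0.92 months, and more if the next 1-2 monthly visit is later.
- Transfer falls after month 12 if weaning is later than 12 - 0.92 = 11.1 to 12 - 0.23 = 11.8 months.
- At referral, "Patients are prescribed one month of treatment". Subtracting that month as well, women weaning after 10.1-10.8 months have no time beyond the supplied month by month 12. With an 18-month end, the cut-off moves to 16.1-16.8 months.

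**How many women.** The Protocol does not say. Section 1 expects the vast majority of those who breastfeed to stop by 6 months, perhaps somewhat later under new guidelines. As an assumption, 5-30% weaning after 10.1-10.8 months gives 195 x 0.05 = 10 to 195 x 0.30 = 59 per arm. The share weaning after 12 months cannot be larger than that.

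**Time after transfer at each horizon.** Arm A transfers at 4-8 weeks = 0.92-1.84 months. An Arm B woman weaned at 6 months transfers at 6.23-6.92 months.
- By 12 months: Arm A 10.2-11.1; Arm B 5.1-5.8.
- By 18 months: Arm A 16.2-17.1; Arm B 11.1-11.8.

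The gap is about 5 months at either horizon.

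**Precision at 18 months.** Assume 25-40% loss, leaving 195 x 0.75 = 146 to 195 x 0.60 = 117 per arm. Use the plan's composite failure rates as stand-ins, since none is given for viral load alone.
- 25% v 10% sustained: 1.96 x sqrt((0.25 x 0.75 + 0.10 x 0.90)/n) = 8.5 points (n=146) or 9.5 (n=117). The 95% CI is 6.5-23.5 or 5.5-24.5.
- No difference at 25%: 1.96 x sqrt(2 x 0.25 x 0.75/n) = 9.9 or 11.1 points.

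**Would the answer move?** Suppose 10% fail regardless of service and the rest accrues evenly after transfer. Then h = ln(0.90/0.75)/(12 - 1.38) = 0.0172 per month. With Arm B transferring at 6 months, failure in Arm A v Arm B is 25.0% v 18.8% at 12 months (6.2 points) and 32.3% v 26.8% at 18 months (5.6 points, from unrounded values). Under this model the extension changes little.

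**The case against.** The strongest reply is that nothing here is contradictory. Horizons are set objective by objective: 2.5.a runs to 18 months, 2.5.e names 6 weeks and 12 months, and 2.5.c names none. Twelve months is the primary time point and a coherent choice. The frequency-and-timing analysis, and the general Kaplan-Meier and cumulative-suppression analyses, have no stated end. The plan also has "secondary analyses stratified by duration of postnatal follow-up in the MCH-ART arm". A curve to first viraemia counts events before weaning too, so it does not isolate suppression after cessation. The extension adds one sample after a doubled interval.

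Most of this stands. It shows that the 12-month curve is legitimate and the gain small. It gives no reason to leave a collected sample out of the curve, because the 12-month estimate can be read from the longer one. The limit of first-event analysis is why an 18-month cross-sectional difference should accompany it.

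A reader might also infer that stopping at 12 months treats the arms unequally, and that 18 months would equalise their time after transfer. The documents do not support this. Objective 2.5.c concerns cessation, which occurs in both arms. The transfer gap is the randomised contrast itself and remains about 5 months at 18 months.

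**Conclusion.** The point holds as a minor one. The survival analysis for objective 2.5.c ends six months before follow-up does and omits one scheduled viral load per woman. For women weaning around or after 12 months, that is the only scheduled sample after cessation and, in Arm B, after transfer. How many such women there are is unknown; section 1 suggests few, since counselling has "all women encouraged to exclusively breastfeed for 6 months" and most are expected to stop by then.

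It would go too far to infer that the 12-month result is invalid, or that the plan excludes the 18-month viral load altogether: the other viraemia analyses have no 12-month limit. At 18 months the trial could tell a sustained 15-point difference from none, but could not resolve 1-5 points. That rests on the assumed 25-40% loss and on composite rates standing in for viral load alone.

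**What to change.** In section 10, Data analysis, change the horizon of the objective 2.5.c survival analysis from 12 to 18 months. Keep the 12-month estimate from the same curve as a landmark. Report the 18-month arm difference in the proportion with viral load below 50 copies/mL, with a 95% CI, as a supportive secondary result.

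No visit, sample or sample-size change is needed. The costs are fewer evaluable women at 18 months and a six-month gap before the last sample, so late viraemia can be placed only between 12 and 18 months; the report should say so.
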